## **8. STUDY INTERVENTION**

### **8.1 Identity of Investigational Products (treatment / medical device)**

Study drug: prednisone vs. matching placebo.

1. Standard (tapering) arm: patients receive 7.5 mg prednisone/d for 7 days; then 5 mg prednisone/d for 7 days; then 2.5 mg prednisone/d for 7 days; then 2.5 mg prednisone every other day for 7 days, then stop.

2. Intervention (abrupt stop) arm: patients receive matching placebo for 4 weeks, then stop.

#### **8.1.1 Experimental Intervention (treatment)**

ICH: Name and description of the investigational product(s).

Placebo:

White placebo tablets containing lactose (P-Tabletten®; diameter 7 mm) will be purchased from Zentiva, Germany. Size, color and divisibility of this product match the 5 mg Prednisone tablet marketed in Switzerland by Galepharm.

#### **8.1.2 Control Intervention (standard/routine/comparator treatment)**

Prednisone:

Prednison Galepharm® p.o., white tablets 5 mg each. Can be broken in half.

#### **8.1.3 Packaging, Labelling and Supply (re-supply)**

Study drugs will be dispensed in a glass vial labeled according to GMP guidelines, annex 13, in German and French language. Each vial will contain 30 tablets, either verum or placebo.

The identification labels contain the unique Participant Study ID and fulfil the requirements of Annex 13 of the "EUDRALEX Volume 4 - Medicinal Products for Human and Veterinary Use: Good Manufacturing Practice". Label text will be available in local language of the countries of each participating centre (i.e., German,).

Dosing:

Week 1: Take one and one half tablets, either prednisone (verum) or placebo, daily p.o.

Week 2: Take one tablet, either prednisone (verum) or placebo, daily p.o.

Week 3: Take one half tablet, either prednisone (verum) or placebo, daily p.o.

Week 4: Take one half tablet, either prednisone (verum) or placebo, on days 1, 3, 5, and 7 p.o.

#### **8.1.4 Storage Conditions**

The study drug is stored at room temperature (15-25°C) in a locked cabinet, separate from routine stocks.

## **8.2 Administration of experimental and control interventions**

### **8.2.1 Experimental Intervention**

Prednisone and other synthetic glucocorticoids are administered in a variety of inflammatory and autoimmune disorders. For most of these, there are no dose regimens that were established in randomized controlled trials, e.g. by head-to-head comparisons. In this trial, therapy of the underlying disease is entirely at the discretion of the treating physician. This includes the decision that the disease is stable and the glucocorticoid is administered at a daily dose that warrants its termination. Our hypothesis that abrupt glucocorticoid stop will not be inferior to tapering, with respect to clinical outcome, can only be tested in a randomized, placebo-controlled trial. Hence we chose placebo as comparator in the experimental arm.

The experimental intervention consists of oral administration of placebo tablets matching those filled with prednisone for 4 weeks. Follow-up is for 6 months after enrolment.

### **8.2.2 Control Intervention**

The control intervention consists of oral administration of prednisone, tablets in decreasing doses, according to the

---

following regimen: patients receive 7.5 mg prednisone/d for 7 days; then 5 mg prednisone/d for 7 days; then 2.5 mg prednisone/d for 7 days; then 2.5 mg prednisone every other day for 7 days, then stop.

There is no consensus in published literature on tapering regimes for any specific disease. An expert committee of Swiss endocrinologists therefore convened and recommended the regimen described above. To be eligible for the trial, a patient must be on a daily dose of 7.5 mg prednisone-equivalent or more, because this is the minimum dosage exceeding the endogenous glucocorticoid production, capable of suppressing the hypothalamic-pituitary-adrenal axis. The drug must have been administered systemically, i.e. orally or intravenously, but not in a depot form (intramuscularly, intraarticularly) or topically, since this would preclude the option to taper in defined dosage steps.

Follow-up is for 6 months after enrolment.

### **8.3 Dose modifications**

The decision to start unplanned open-label glucocorticoid therapy during the blinded treatment phase or during follow-up rests with the treating physician or the patient, not the study team. Indication to do so include flare-up of the underlying disease, symptoms and signs of cortisol deficiency such as weakness, apathy, nausea, vomiting, abdominal pain, hyperthermia, hyponatremia, hyperkalemia, hypoglycemia, or adrenal crisis (i.e. glucocorticoid-responsive shock) (see also section 8.6. below). Should the study physician suspect the necessity of open-label glucocorticoid therapy during follow-up, he/she will contact the treating physician to prompt a visit.

### **8.4 Compliance with study intervention**

Patients will be asked to fill out a medication diary over the 4-week treatment phase. Adherence to study medication will be ascertained during the follow-up telephone visits at days 7 and 35 when patients will be asked to count tablets remaining in the vials ("pill count"). All patients will be asked to send back the spare tablets at the end of the treatment phase or return them at the visit on day 35, if this is a hospital visit. A sensitivity analysis will be performed to determine a compliance cutoff, i.e. a critical percentage of ingested study medication, below which an association with the outcome is visible.

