### 11.2 Determination of Sample Size

To assess the primary outcome measure, a Cox proportional hazards regression model will be fitted to the data. Non-inferiority will be concluded if the two-sided 95% confidence interval of the hazard ratio between the experimental and the control arm lies entirely below the critical hazard ratio defined as

$$HR = \frac{\lambda_e}{\lambda_c} = \frac{\frac{-\log(\pi_{et})}{t}}{\frac{-\log(\pi_{ct})}{t}} = \frac{\log(\pi_{et})}{\log(\pi_{ct})} = \frac{\log(\pi_{ct} - m)}{\log(\pi_{ct})}$$

where  $\lambda_e$  and  $\lambda_c$  are the hazard rates in the experimental and control arms,  $t$  is a fixed point of time,  $\pi_{et}$  and  $\pi_{ct}$  are the proportions of event-free patients at time  $t$ , and  $m$  is the non-inferiority margin expressed as the additional proportion of patients having had an event in the experimental arm, assuming that the occurrence of events follows an exponential distribution. Noninferiority will be concluded if the upper limit of the two-sided 95% confidence interval of the hazard ratio lies below the critical hazard ratio.

For the sample size estimation, the following assumptions were made:

- Patients are randomized to the control and experimental arms in a 1:1 ratio.
- After inclusion, all patients are followed for 6 months. Patients without an event within 6 months are considered right-censored and are not followed any further even though the trial might be ongoing.
- 10% of patients drop out within the 6 months follow-up period. The drop-out events are distributed uniformly over this period.
- The event rate within the 6 months follow-up period, i.e., the proportion of patients with an event, is 40%, both for the control and the experimental arms. We estimated this overall figure based on expected relapse rates for the various eligible diseases, as indicated by clinical experts and published data, e.g. in COPD or inflammatory bowel disease. Our estimation is conservative since the other components of the combined primary outcome will contribute to the event rate.
- The survival curves in the control and experimental arms follow the same exponential distribution. The rate parameter of the exponential distribution is chosen so that the corresponding cumulative distribution function value at 6 months equals the assumed event rate.

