- The non-inferiority margin is defined as an absolute increase of the event rate by 13% over 6 months. We used a modified Delphi approach to determine this margin. 10 experienced clinicians board-certified in internal medicine and/or rheumatology, gastroenterology, and endocrinology were individually asked to define the maximum increase in outcome events they would accept for the benefit of rapid glucocorticoid stop and gain of high-quality scientific data in the area of steroid withdrawal. Assuming an event rate of 40% in the standard treatment arm, the mean tolerable increase under experimental treatment was 13.6% (range, 5 to 20%; median, 13%).
- The significance level is 5%.

For each combination of the noninferiority margins 7.5%, 7.6%, ..., 17.5%, and the sample sizes  $n = 200, 210, \dots, 1200, 999$  individual data sets were simulated based on the above assumptions. A Cox proportional hazards regression model was fitted to each data set, and the hazard ratios for the experimental vs. the control arm with the associated 95% confidence interval were estimated. Noninferiority was concluded if the upper limit of the two-sided 95% confidence interval of the hazard ratio was below the critical hazard ratio (see above equation). The power was estimated as the proportion of positive conclusions divided by the total number of the 999 iterations per parameter combination. To achieve a power of 80%, 573 patients (95% CI, 565 to 580) need to be included, assuming an event rate of 40% over the 6 months follow-up period and setting the non-inferiority margin to 13% (Figure). The critical hazard ratio for this noninferiority scenario is 1.478.

The sample size of  $n=573$  is a conservative estimation, since the assumed drop-out rate of 10% is relatively high.

[figure not shown]

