#### 11.4.1 Datasets to be analysed, analysis populations

The full analysis set (FAS) consists of all patients who are randomised.

The intention-to-treat (ITT) set is a subset of the FAS that consists of all patients for whom the primary endpoint is available. Patients are assigned to the treatment arm they are randomised to.

The per protocol (PP) set includes the same patients as the ITT set, but patients are assigned to the treatment arm that corresponds to the actually obtained treatment.

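### Section 8.4 picks the compliance cutoff by looking at the outcome, so this sensitivity analysis, and anything that reuses its cutoff, can show an association that does not exist

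*Protocol*

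**What the plan says.** Protocol section 8.4 describes a medication diary over the four-week treatment phase, pill counts and return of spare tablets. "Adherence to study medication will be ascertained during the follow-up telephone visits at days 7 and 35"; section 9.3.4 adds a pill count in the day 28 interview. Section 8.4 then announces a sensitivity analysis "to determine a compliance cutoff, i.e. a critical percentage of ingested study medication, below which an association with the outcome is visible". It gives no percentage, list of candidate cutoffs, test, or definition of visible.

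No other numeric compliance threshold appears. In section 11.4.1 the per-protocol (PP) set holds the same patients as the ITT set, but "patients are assigned to the treatment arm that corresponds to the actually obtained treatment". Section 11.4.2 runs the primary analysis on that set. Section 7.4 names non-compliance as a reason for excluding a patient, without a threshold.

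**The concern.** Two separate mechanisms can produce a critical percentage when compliance has no effect.

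- **Selection on the endpoint.** If several cutoffs are tried and the one showing an association is kept, the chance of a false finding exceeds that of a single planned comparison.
- **Reverse causation.** Under sections 5.1 and 8.3, unplanned open-label glucocorticoid can start during the blinded phase and is itself a primary event; hospitalisation and death are others. A patient with such an event may leave tablets untaken, and the count at day 28 or 35 comes after it. Early events then collect among patients with low counts.

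At stake is the meaning of the only compliance analysis that the protocol describes. In a noninferiority trial poor adherence can make the arms look alike, so readers will want a sound view of adherence.

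**Working it through.** **1. The plan's own figures.** Section 11.2 supplies the design. Both arms are given a 40% event risk at six months. On the margin it says: "The non-inferiority margin is defined as an absolute increase of the event rate by 13% over 6 months". The decision rule sets the upper two-sided 95% limit for the hazard ratio against a critical value, and 573 patients are planned for 80% power.

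- Critical hazard ratio: ln(0.60 − 0.13)/ln(0.60) = 0.755/0.511 = 1.478, as stated.
- Events (Schoenfeld, two-sided 5%, 80% power): 4 × (1.960 + 0.842)² / (ln 1.478)² = 205.7, so 206.
- Patients: 206/0.40 = 515; 515/0.90 = 572.2, so 573, as stated.

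The sample size is not in question. It provides n = 573 and a 40% event risk for the check below.

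**2. Searching cutoffs with no true association.** Ten independent tests at 5% would give 1 − 0.95¹⁰ = 40%. Neighbouring cutoffs are correlated, so simulation is needed. The compliance distribution, the grid and the p < 0.05 rule are assumptions, since the protocol gives none. The table shows the share of null trials with at least one nominally significant cutoff.

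| Assumed compliance (mean) | 50–95% in steps of 5 | 70/80/90 | 80/90 | Fixed 80% |
|---|---|---|---|---|
| Beta(6, 1.2) (6/7.2 = 83%), log-rank, 2,000 trials | 27.6% | – | – | 5.4% |
| Beta(6, 1) (6/7 = 86%), two-proportion test, 4,000 trials | 25.3% | – | – | 4.5% |
| Beta(6, 1), separate run, 3,000 trials | 28% | 12% | 8% | – |
| Beta(20, 1) (20/21 = 95%), 3,000 trials | 16% | 8% | 8% | – |
| Beta(30, 0.8) (30/30.8 = 97%), 3,000 trials | 9% | 5% | 5% | – |

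A further run over such assumptions gave about 4% to 29%, with about 5% or less at a fixed 80%.

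**3. Reverse causation.** Under the plan's exponential model the risk of an event before day 28 is 1 − 0.6^(28/182.4) = 7.5%, or about 43 of 573 patients. From the dosing in section 8.1.3, tablets due are 7 × 1.5 + 7 × 1 + 7 × 0.5 + 4 × 0.5 = 23. A fully adherent patient who stops at an event would score:

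- day 7: 10.5/23 = 46%
- day 14: 17.5/23 = 76%
- day 21: 21/23 = 91%

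Perfect adherence up to a day 14 event thus falls below an 80% cutoff. Suppose half of the patients with an event before day 28 stop tablets then (assumption), with Beta(6, 1.2) compliance and intake cut in proportion to time. An association then appears in 43% of null trials at a fixed 80% cutoff and in over 99% with the ten-step search. Across stopping shares of 25% to 50%, the ten-step search gives about 66% to 100%. Fixing the threshold alone is therefore not enough.

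**4. The comparison between arms.** In the log-rank simulation, where compliance is unrelated to arm, a cutoff chosen on pooled data leaves the error of the arm comparison among compliers at about 5%. A cutoff chosen on the arm effect itself raises it to about 15%. Section 8.4 speaks of association with the outcome and does not say whether the search is pooled or by arm.

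**The case against.** The strongest reply is that no decision rests on the cutoff. Section 8.4 calls the exercise a sensitivity analysis, nothing in section 11.4 applies its result, and no Cox comparison restricted to compliers is planned. This stands, and it limits the reach of the point.

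The size is also soft. The protocol states no grid, test or compliance distribution; with high compliance and few cutoffs the inflation nearly vanishes. This stands too, so only a range is justified.

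Reverse causation is partly conjecture, because no section says that study tablets stop when open-label treatment starts. That is fair, and the step 3 figures are conditional on it. But events before day 28 are expected, and the final count follows them.

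Finally, section 11.4 leaves detail to an analysis plan that is not at hand. That does not answer the point: section 8.4 already states a method, and the method is unsound.

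A reader might infer that the primary noninferiority conclusion is compromised, that every compliance-based analysis is biased, or that 25% is the error rate of the treatment comparison. The documents support none of these. The PP set removes nobody for low compliance, an analysis with a threshold set in advance would not be outcome-driven, and the 25% concerns the compliance-outcome association under one set of assumptions.

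**Conclusion.** The point holds in limited form. The rule in section 8.4 selects the cutoff on the endpoint and can return a critical percentage when compliance has no effect.

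The false-positive chance for that association is roughly 4% to 29% from searching alone. It is much higher if some patients with early events leave tablets untaken. Both figures rest on assumed compliance distributions and grids, and the second also on an assumed stopping share.

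The primary test is unaffected as written. The damage would spread only if the cutoff were reused, for instance to define compliers in an arm comparison or to give a threshold to the non-compliance exclusion in section 7.4. Nothing in the protocol links the cutoff to either. The correction is worth making but does not threaten the main result.

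**What to change.** Replace the sentence in section 8.4, and carry the replacement into the analysis plan:

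- State one compliance threshold, or a small set that will all be reported, fixed before unblinding and without reference to outcome. The 80% used above is illustrative.
- Calculate compliance from diary and pill counts, over tablets due up to the earlier of day 28 or the first primary event.
- Label any compliance-outcome relation, and any Cox analysis restricted to compliers, as a supportive sensitivity analysis.

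The cost is one sentence in the protocol and an entry in the analysis plan; the diary, pill-count and returned-tablet data are already collected. There are three downsides. Any threshold is conventional. Intake up to an event depends on the self-completed diary, because pill counts fall only at scheduled contacts. Restricting to compliers remains a selection made after randomisation, so it can support the primary result but not replace it.

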### **8.5 Data Collection and Follow-up for withdrawn participants**

Patients who choose to withdraw from the study during the treatment intervention will be considered as drop-outs. Patients who choose to withdraw from the study during the follow-up period (i.e. refuse to participate in the telephone interviews on days 35, 90, and 180 or to come to the outpatient visit on day 35, if applicable) will be asked for permission to contact their treating physician for inquiry of the 1° outcome and to use their data collected so far. This will prevent their drop-out. If patients do not permit the inquiry of the 1° outcome, their data will be considered right-censored from the last documented contact onward.

### **8.6 Trial specific preventive measures**

Each study participant will be given five 10 mg tablets of prednisone for open label/rescue therapy in case of urgent need for glucocorticoid administration. Each study participant will be instructed about the signs and symptoms of glucocorticoid deficiency upon enrolment and will receive a written document specifying these signs and symptoms in a well understandable manner (see screen 6.11, "Stressprophylaxe").

Open label or rescue glucocorticoid therapy will be recorded on the CRF. Its impact on the study is such that unplanned glucocorticoid therapy is one of the components of the primary, as well as one of the secondary outcomes.

### **8.7 Concomitant Interventions (treatments)**

Any concomitant care or/and intervention is at the discretion of the treating physician and will be recorded on the CRF. If such care/intervention leads to hospitalization, it will affect the trial as component of the primary as well as one of the secondary outcomes. Any concomitant care and interventions will be recorded in the CRF.

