
Die vorliegende Studie soll deshalb die Hypothese prüfen, dass auch nach längerer Behandlungsdauer mit Prednison (mindestens über 4 Wochen mit insgesamt mindestens 420 Milligramm) das Medikament abrupt gestoppt werden darf, ohne dass dadurch ein schlechterer Verlauf resultiert. Die Beobachtungsdauer ist 6 Monate nach Studieneinschluss. Um eine genügende Aussagekraft zu erhalten, werden 573 Patienten für die Untersuchung benötigt, wovon die Prednisonbehandlung bei der einen Hälfte über vier Wochen ausgeschlichen und bei der anderen abrupt gestoppt wird. Teilnehmer der letzteren Gruppe erhalten statt Prednison gleich aussehende Schein-Präparate (Placebo). Über die Gruppenzuteilung entscheidet der Zufall, und weder Teilnehmer noch Prüfarzt kennen die Gruppenzugehörigkeit (Doppelblind-Prinzip). Zur Beurteilung des Verlaufs wird in beiden Gruppen die Zeit verglichen, die verstreicht bis zum erstmaligen Auftreten eines oder mehrerer der folgenden Ereignisse: Hospitalisation, Anzeichen eines Cortisolmangels, Tod, oder ungeplante Wiederbehandlung mit Prednison oder einem anderen Cortisol-ähnlichen Medikament (zum Beispiel wegen eines Rückfalls der ursprünglich mit Prednison behandelten Krankheit). Es soll zudem untersucht werden, ob der Synacthentest geeignet ist, das Auftreten dieser Ereignisse vorherzusagen. An alle Teilnehmenden werden sicherheitshalber Prednison-tabletten abgegeben; diese sind in Situationen mit erhöhtem Cortisolbedarf, zum Beispiel bei fieberhaften Erkrankungen, einzunehmen (sog. Stressprophylaxe).

Dies ist die erste Studie überhaupt, in der das Absetzen von Prednison mit einem Ausschleich-Schema direkt verglichen wird. Bestätigt sich die Studienhypothese, kann künftig auf die unnötige Verlängerung von Prednisonbehandlungen verzichtet werden, was angesichts des ungünstigen Nebenwirkungsprofils wünschbar wäre. Falls sich zeigt, dass das abrupte Stoppen doch Nachteile hat gegenüber dem Ausschleichen, gäbe es auch für letzteres Vorgehen erstmals eine wissenschaftlich fundierte Grundlage.

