### 3.6 Explanation for choice of comparator (or placebo)

Although ideally chosen for the standard arm in a noninferiority trial, there is no published standard, “best-of-care” glucocorticoid tapering scheme, but a large variety of expert opinions. Accordingly, for many inflammatory and autoimmune disorders, there are no specific guidelines as to the tapering regimens. Also, there are no controlled data indicating the superiority, with respect to clinical outcome of the underlying disease, of one particular tapering scheme over another, or of tapering versus abrupt stopping. These facts and our own observations in COPD patients with biochemically suppressed adrenal glands have led us to hypothesize that, in patients chronically treated with glucocorticoids, the clinical outcome will not be worse if glucocorticoids are stopped abruptly than if they are tapered over as long as 4 weeks. This hypothesis can only be tested in a randomized, placebo-controlled trial. Hence we chose placebo as comparator. This is ethically justifiable because the dangers of clinically relevant secondary adrenal failure are small (see chapter 3.1. above). Should signs and/or symptoms of glucocorticoid deficiency nevertheless occur, or should the patient encounter circumstances with increased needs for glucocorticoids (e.g. an acute illness) or undergo a stressful procedure (e.g. an operation), glucocorticoid cover is given as per protocol.

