### 3.7 Risks / Benefits

Potential risks:

In the standard treatment (prednisone) arm, the potential risks are those of unwarranted and prolonged glucocorticoid therapy, in particular: weight gain, osteopenia/osteoporosis, hyperglycemia, hypertension, muscle catabolism, increased susceptibility to infections due to immunosuppression, and suppression of the endogenous cortisol production by the adrenals.

In the intervention (placebo) arm, there is a potential risk of flare-up of the inflammatory disorder (although this is not based by high-grade evidence), and of unforeseen glucocorticoid requirements, be it due to flare-up of the underlying disease, glucocorticoid deficiency, or glucocorticoid withdrawal syndrome. The risk of endangering the patients is offset by the ease of glucocorticoid stress prophylaxis and cover in case of signs and symptoms of hypocortisolism, for which patients will be instructed and provided with an emergency dose of five 10 mg tablets of prednisone.

Trial participants in both treatment arms may be at risk for severe courses of coronavirus disease-19 (COVID-19), be it due to immunosuppression following longstanding glucocorticoid treatment prior to study enrolment, or due to iatrogenic hypocortisolism, or both. While COVID-19 vaccination is not mandatory for trial participation, patients should be encouraged to undergo vaccination. All participants are carefully instructed regarding emergency glucocorticoid therapy. This so-called stress prophylaxis should also be taken by the patient should post-vaccination symptoms of viral disease occur, but not routinely in order not to jeopardize efficacy of the vaccine. The “TOASST” trial will be conducted in accordance with all current instructions by the competent authorities.

Potential benefits:

The main overall benefit of this trial is the generation of high-level evidence about the feasibility and safety of rapid glucocorticoid withdrawal in comparison with a tapering regime, as no published data on this topic exists from randomized controlled trials.

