## 5. STUDY OUTCOMES

### 5.1 Primary Outcome

The composite primary outcome is:

Time to first occurrence of hospitalization, death, initiation of unplanned systemic glucocorticoid therapy, or adrenal crisis (defined as glucocorticoid-responsive hypotension or shock with or without accompanying symptoms and signs such as weakness, apathy, nausea, vomiting, abdominal pain, hypothermia, hyponatremia [serum sodium < 135 mM], hyperkalemia [serum potassium > 5 mM], hypoglycemia [plasma glucose < 3.5 mM]); whichever occurs first.

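### The primary endpoint counts planned admissions and leaves open whether instructed stress cover is an event, so events unrelated to the arm can blunt the noninferiority comparison

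*Protocol*

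**What the plan says.** **Hospitalization.** Section 5.1 defines the endpoint as "Time to first occurrence of hospitalization, death, initiation of unplanned systemic glucocorticoid therapy, or adrenal crisis". The word *unplanned* attaches only to the glucocorticoid component. Section 8.7 covers any concomitant care given at the treating physician's discretion and adds: "If such care/intervention leads to hospitalization, it will affect the trial as component of the primary as well as one of the secondary outcomes". No section excludes elective or pre-booked admissions, and the questionnaire in 9.2.1 simply asks whether the patient was hospitalized.

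**Glucocorticoid cover.** Several passages describe cover that patients are told to take:
- Section 3.6, on acute illness or an operation: "glucocorticoid cover is given as per protocol".
- Section 3.7, on vaccination: "This so-called stress prophylaxis should also be taken by the patient should post-vaccination symptoms of viral disease occur".
- The local-language summary, on the dispensed tablets: "diese sind in Situationen mit erhöhtem Cortisolbedarf, zum Beispiel bei fieberhaften Erkrankungen, einzunehmen" (they are to be taken when cortisol need is raised, for example in febrile illness).

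Section 8.6 issues those tablets, has open-label or rescue use recorded, and states that "unplanned glucocorticoid therapy is one of the components of the primary, as well as one of the secondary outcomes". Sections 7.4 and 8.3 describe unplanned treatment mainly as a response to flare, symptoms of deficiency or adrenal crisis.

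**Decision rule.** Section 11.1 states the hypothesis on the composite. Section 11.4.2 fixes the limit at a hazard ratio of 1.478. Section 11.2 takes the 40% event rate from expected relapse rates and calls it conservative because the other components add events.

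**The concern.** A joint replacement booked before enrolment cannot be a consequence of the allocated regimen, yet it ends the patient's time at risk in the primary analysis. A course of cover taken because the protocol told the patient to take it may do the same, depending on how a site reads *unplanned*. Two sites could code the same tablets differently.

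In a superiority trial such events mostly cost power. In a noninferiority trial they move the hazard ratio toward 1, which is the direction of the claim. The remark in 11.2 that further components make the 40% conservative is true for the number of events. It does not hold for the ability to see harm. The sample size re-estimation in 11.4.4 does not help either, because it changes only the number of patients. The analysis is also of the first event, so an unrelated admission or cover course pre-empts a later relapse.

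**Working it through.** **Inputs from the protocol (11.2, 11.4.2).** Event rate 40% at 6 months in both arms; margin 13 points; exponential times; 1:1 allocation; N = 573; 10% drop-out spread evenly; upper limit of the two-sided 95% interval below the critical hazard ratio.

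**The plan's own figures.**
- Critical hazard ratio: ln(0.60 − 0.13)/ln(0.60) = ln 0.47/ln 0.60 = 0.7550/0.5108 = 1.478, as stated.
- Events for 80% power: 4 × (1.960 + 0.842)²/(ln 1.478)² ≈ 206. Then 206/0.40 = 515, and 515/0.9 gives 573, as stated.
- A Cox simulation on the plan's assumptions with 573 patients gives 81.7% power (4,000 runs). The sample size is not in question.

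**Input the documents do not give.** The proportion q of patients with an event unrelated to the arm over 6 months is an assumption. Here q comes on top of the 40%, which matches how 11.2 describes the rate.

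**Method.** Place the relevant events exactly at the limit (40% against 53%) and add the same hazard −ln(1 − q) to both arms:

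composite HR = [0.7550 − ln(1 − q)] / [0.5108 − ln(1 − q)]

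- q = 5%: (0.7550 + 0.0513)/(0.5108 + 0.0513) = 1.434
- q = 10%: (0.7550 + 0.1054)/(0.5108 + 0.1054) = 1.396

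The probability of declaring noninferiority is Φ{[ln 1.478 − ln(composite HR)]/SE − 1.96}, with SE = √(1/e_c + 1/e_e). The event counts e_c and e_e use 286.5 patients per arm, less about 4.5% of events lost to drop-out.

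- q = 5%: rates 43.0% and 55.35%, events about 118 and 151, SE 0.123, Φ(−1.72) = 4.3%
- q = 10%: rates 46.0% and 57.7%, events about 126 and 158, SE 0.119, Φ(−1.48) = 6.9%

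| Assumed q | Composite HR | Noninferiority declared (formula) | Same, by simulation (3,000 runs) | Excess of relevant events when the composite sits at 1.478 |
|---|---|---|---|---|
| 0% | 1.478 | 2.5% | 2.4% | 13.0 points |
| 5% | 1.434 | 4.3% | 4.6% | 14.1 points |
| 10% | 1.396 | 6.9% | 6.8% | 15.3 points |
| 20% | 1.333 | not computed | 14.6% | 17.8 points |

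A separate simulation of 4,000 runs at q = 0 gave 3.2%, so differences of under a percentage point should not be read closely.

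If the unrelated events are instead part of the 40% and make up 10%, 20% or 30% of the control hazard, the composite HR is 1.430, 1.382 or 1.335. Noninferiority is then declared in 4.8%, 8.4% or 12.5% of simulated trials.

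**Why starts should be split by reason.** Suppose 40% relapse in each arm and treatment for adrenal insufficiency triples from 2% to 6% (assumed figures). The composite is 1 − 0.60 × 0.98 = 41.2% against 1 − 0.60 × 0.94 = 43.6%. The HR is ln 0.564/ln 0.588 = 1.08, and noninferiority is declared with probability about 0.67. No planned admission or stress cover enters this example. It shows only that a rare component is invisible in the composite and must be read separately.

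**The case against.** **The margin belongs to the composite.** This is the strongest reply. A reader might take the 4% to 7% as inflated type I error. The documents do not support that. Section 11.1 puts the hypothesis on the composite, and the Delphi question in 11.2 asked about outcome events overall. At q = 5% and 10% the composite differences are 55.35 − 43.0 = 12.35 points and 57.7 − 46.0 = 11.7 points. Both are inside 13 points with hazard ratios below 1.478, so a noninferiority conclusion there is correct for the hypothesis as written. The composite hazard ratio is estimated without bias. This objection stands, and the loss is one of sensitivity.

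**Instructed cover may not count.** A reader might infer from 8.6 that every dispensed tablet taken is a primary event. The text does not go that far. Sections 7.4 and 8.3 point toward flare and deficiency, although 8.3 does not present its list as complete. What stands is that the question is unsettled.

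**Cover and admissions may depend on arm.** Section 3.7 names susceptibility to infection as a risk of the prednisone arm, so febrile illness and its cover need not be neutral. Treating all such events as noise would be wrong. All-cause hospitalization also avoids causal judgement and is a defensible choice.

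**Much is already separated.** Components are analysed individually (5.2 item 1, 11.4.3), and glucocorticoid dose is split by purpose (5.2 items 3 and 4). Yet the time-to-start analysis still merges all reasons, and item 3 pools treatment with prevention.

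**Conclusion.** The point holds as a defect of endpoint definition. Under 5.1 and 8.7 as written, admissions arranged before randomisation are primary events. This follows from the unqualified wording, since no section names planned admissions. Whether instructed cover is an event cannot be determined from the protocol.

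To the extent that such events are unrelated to the arm, they reduce the trial's ability to detect harm from an abrupt stop against a fixed limit of 1.478. With an assumed 5% to 10% of patients affected, a relevant hazard ratio of 1.478 appears as about 1.43 to 1.40, and noninferiority is declared in about 4% to 7% of trials. The size rests on that assumed share, on exponential times and on true independence from arm. The documents establish the direction but not the size. Neither the sample size nor the type I error for the composite hypothesis is at fault. The change is advisable and cheap.

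**What to change.** 1. **Admissions.** In 5.1 and 8.7, exclude admissions scheduled before randomisation. Classify them blind to arm from the SAE form, since 10.1.1 and 10.1.2 already route hospitalizations there. Keep all-cause hospitalization as a sensitivity analysis. If the sponsor prefers to keep all-cause hospitalization as primary, prespecify the restricted version as the sensitivity analysis.
2. **Cover.** Reconcile 3.6, 3.7, 7.4, 8.3 and 8.6, together with the local-language summary, on whether instructed cover counts as unplanned for the endpoint. This concerns coding only and leaves the instructions to patients untouched. Record the reason for each open-label start: relapse, symptoms of deficiency, or cover for an external stressor. Add a sensitivity analysis without external-stressor cover, and state that infections may depend on arm, so this analysis supports the primary one and does not replace it.
3. **Reporting.** In 5.2 item 1, report time to first glucocorticoid start separately for relapse and for adrenal insufficiency. Section 9.2.2 already asks treating physicians for dose by purpose.

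**Cost.** Amendment wording, one CRF field for reason and planned status, a blinded classification step, and slightly fewer primary events. Because 11.2 built the 40% from relapse rates, the sample size does not rely on planned admissions. Recruitment began in 2017, so the change should be made while the comparison is still blinded, and earlier admissions should be classified by the same rule.
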